#### Aim 1 Recruitment

Participants are recruited via RDS, given demonstrated benefits to (1) potentially recruit a more representative sample and (2) reach deep into social networks to recruit participants who are often not reached through outreach, venue-based, or snowball sampling methods for engagement in HIV testing [6,7,9]. In this method, 8 to 10 MSM and TW seeds will be recruited by study investigators. Seeds, who begin recruitment, are individuals who represent a range of characteristics and are well-networked within the MSM and TW population. The study team works with local CBO partners in Yangon to identify MSM and TW seeds. Seeds complete the first visit study activities and are then given a maximum of 3 coupons with which to recruit their peers from within their social or sexual networks. These peers are invited by the seed to present to the study office with their coupon for participation in the study. If eligible and after completing baseline study activities, the recruited participant may, in turn, become a recruiter. Participants who agree to become a recruiter undergo recruitment training and receive a maximum of 3 coupons for distribution. This process continues until the sample size has been reached. This sampling method has been successfully used by the research team for several research studies of HIV among MSM, including in Malawi and Russia [7,39,40]. RDS has also been used by other investigators to research HIV among people who inject drugs, MSM, and TW in Myanmar [41,42].

Recruitment coupons are prenumbered with a unique coupon number prior to distribution (Figure 3). Coupons contain other information including the study telephone number, site operating hours, and coupon expiration date. There is no information on the coupon that could be used to identify the holder as MSM or TW and no personal information is recorded on the coupon. Coupons are collected from recruited candidate participants at the study site at the time of eligibility screening and the returned coupon number is recorded. Coupons allow for the research team to trace the recruitment process and create analytical weights for the sampling process.

**Figure 3 figure3:**
[figure not shown]
Respondent-driven sampling coupons (front and back).

#### Aim 1 Data Collection

Eligible participants recruited through the RDS are verbally consented using paper-based consent forms in private rooms within the study office. Upon providing consent, participants complete a structured, 30- to 45-minute interviewer-administered, tablet-based questionnaire, which serves as the baseline assessment. The questionnaire allows for comparison of HIVST versus clinic-based testers and attrition analysis of those who return versus do not return for their follow-up visit. Measures in this questionnaire include demographic and network characteristics, previous testing history and experiences, sexual and substance use risk profiles, access to HIV and sexually transmitted infection prevention and care, measures of perceived and experienced stigma in health care settings, concerns over police or other security harassment, and factors related to cost, distance, convenience of testing venues, and acceptability of assigned testing method. Individual network size measures, commonly collected for the analysis of RDS data, assess the number of MSM and TW in the Yangon area the participant knows and has seen or spoken to in the last 6 months. The questionnaire also includes 2 of 5 parameters recommended by Pant Pai et al [15] for HIVST assessments, specifically acceptability of testing methods and motivations for HIVST among users.

Following the questionnaire, pretest counseling is administered prior to collection of dried capillary blood spot collection (DBS) via a finger prick. DBS is analyzed at a local reference lab in Yangon. The primary purpose of DBS collection is to ensure that the study team receives HIV test results for any participants who do not return to the clinic for their follow-up visit. The DBS will also confirm clinic-based HIV test or preliminary HIVST results during visit 2, allowing for further validation of the self-testing and clinic-based results.

Following pretest counseling, participants will be electronically randomized to clinic-based VCT or HIVST. Participants assigned to VCT are provided with referral information for partner clinics and instructed to complete clinic-based HIV testing services within 2 weeks. Individuals randomized to HIVST will be provided with the OraQuick in-Home HIV Test (OraSure Technologies) self-testing kit and instructions for use. OraQuick in-Home HIV Test is an FDA-approved oral HIV test that allows the user to self-administer the salivary test in private and displays results within 20 minutes. The OraQuick in-Home HIV Test tests for HIV-1/2 antibody test and has a sensitivity of 91.7% and specificity of 99.9%. The test is recommended for use as a method to screen for HIV infection to be followed with confirmatory testing. Johns Hopkins University (JHU) has partnered with OraSure to provide Myanmar language instructions within the kit. Participants randomized to HIVST are instructed to complete HIVST any time before their scheduled second visit. HIVST participants are provided with a study telephone number that they can call for assistance at any time of day.

All participants are instructed to call the project office immediately if they receive a preliminary positive HIV test result. Study staff schedule these participants to return to the project office for visit 2 as soon as possible. This ensures that all participants are offered posttest counseling, confirmatory testing, and enrollment in Aim 2 (CD4 POC staging) as quickly as possible. DBS analysis is expedited for participants who cannot be reached or who do not disclose their HIV testing results. HIV testing is considered complete when participants have received results from their assigned method of testing and report awareness of their HIV status.

#### Aim 1 Follow-Up

All participants are scheduled for a second visit 2 to 3 weeks after the primary visit. During this visit (visit 2), self-reported VCT and HIVST results are ascertained. Analysis of DBS specimens is conducted between visit 1 and 2 to serve as confirmatory testing of results identified through clinic-based VCT or HIVST. Special effort are made to recontact, counsel, and provide appropriate referrals for participants who do not return for the follow-up visit but who are identified with HIV infection during analysis of DBS. Participants found to be preliminarily HIV-negative are given posttest counseling, which includes an explanation of the test result, advice on risk reduction, and the provision of condoms, lubricant, and referrals. These participants are advised to seek HIV testing again in 3 months and are provided with contact information for local nongovernmental organizations who provide HIV testing and care services to MSM and TW. Participants confirmed HIV infected are given posttest counseling and offered enrollment in Aim 2 to conduct immediate CD4 POC staging. Participants who decline enrollment in Aim 2 are provided with referrals for standard CD4 testing as well as treatment and care services. Participants with discordant DBS and self-reported HIVST or VCT results are asked to provide an additional blood sample for confirmation by Western blot.

All participants are asked to complete a structured, 30-minute interviewer-administered questionnaire during visit 2 that serves to evaluate uptake and acceptability of clinic-based or HIVST methods. Participants also receive secondary reimbursement for recruitment of peers at the second visit, which is a standard practice of RDS and will incentivize this follow-up visit.

#### Aim 1 Analytical Approach

Baseline characteristics are analyzed using a program written for Stata (StataCorp LLC), which makes statistical adjustments for RDS sampling to characterize unbiased asymptotic estimates of disease burden and other characteristics by weighting for social network size (RDS-II estimator) [43]. Exploratory analysis is conducted to evaluate recruitment depths and potential biases induced by recruitment [7]. Results include descriptive statistics related to sociodemographic characteristics, knowledge of STI/HIV, and sexual behavior and attitudes of MSM and TW populations. Bivariate and multivariable analyses using multiple logistic regression or log binomial regression, depending on the calculated prevalence [44], are performed to determine the association between HIV infection and key behavioral outcomes and other variables. Additional analysis focuses on the parameters recommended by Pant Pai et al [15] for HIVST assessments, conducting a stratified analysis of acceptability of testing methods, accuracy, concordance with health care worker testing, feasibility and motivations for testing among consumers, and comparability of HIVST to VCT.

The primary hypothesis for this continuum innovation step is that a higher proportion of persons who are randomized to HIVST will complete HIV testing than those randomized to standard clinic-based testing. Given the randomized nature of the study design, the study team will use a standard comparison approach to assess the outcomes of the 2 intervention arms for this aim. Standard contingency tables with Fisher exact test for significance is used to evaluate the efficacy of the intervention. A comparison of intervention arms (HIVST vs clinic-based) is the primary outcome measure, and balance in potential measured confounders is assessed. Implementation measures of HIV testing include uptake of HIV testing services, fidelity of the implementation of the intervention, and acceptability of HIV testing options.

Attrition analysis is conducted to assess the potential differential loss to follow-up by individual characteristics (demographics, sexual identity, and distance from office/clinic) as well as assigned intervention groups. Where possible, we attempt to recontact participants to understand individual reasons for failed return, which is particularly important during the start-up of the interventions, in which logistical changes can be made to address losses to follow-up. Any logistical changes are documented.

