#### Aim 1 Study Sample

Aim 1 participants are included on the basis of the following inclusion criteria: assigned male sex at birth, aged 18 years or older, reports having had any type of sex with another man in the past 12 months, presents to the study with a valid RDS coupon (except seeds), speaks Myanmar, currently a resident of the greater Yangon area, is mentally sound and capable of providing consent to participate, and has provided informed consent to participate in the study. Participants who have been tested for HIV within the last 6 months or who are known to be living with HIV infection are excluded from participation in Aim 1. However, individuals who disclose a positive HIV status when Aim 1 eligibility is determined are considered for enrollment in Aims 2 and 3, provided they meet all eligibility criteria for those aims. While there are emerging and increasingly open gay communities in Yangon, the traditional categories of sexual orientation and gender identity in Myanmar culture are blurred; locally, the term MSM is often used interchangeably across male and transgender-identified populations and these groups often attend similar community-based events [38]. Thus, this study focused on the inclusion of both MSM and TW populations.

The target sample size needed for the RDS sample is 366 MSM and TW participants. This estimate achieves 2 goals. First, it allows for a comparison of HIVST versus clinic-based HIV testing. Assuming an error of .05 and 80% power to detect a 15% difference in acceptability between the 2 testing methods (60% acceptability of clinic-based testing and 75% acceptability of self-testing), a sample of 330 (or 165 per group) is needed. Upon factoring a 10% nonresponse in both testing methods, an effective sample size of 366 MSM and TW participants is calculated. Second, this allows for subsequent enrollment of MSM and TW participants into Aims 2 and 3. Assuming a conservative 15% prevalence of HIV among the sample [28], this identifies 54 participants who are then eligible for Aims 2 and 3.

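### Weighted Aim 1 estimates are called unbiased for HIV burden among MSM and TW, but the exclusions limit them at best to undiagnosed HIV in people not recently tested

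*Protocol article*

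**What the plan says.** Under Aim 1 Analytical Approach, baseline data are adjusted for the sampling method "to characterize unbiased asymptotic estimates of disease burden and other characteristics by weighting for social network size (RDS-II estimator". The same paragraph says the results include "knowledge of STI/HIV, and sexual behavior and attitudes of MSM and TW populations", with no narrower population named, and plans regressions of HIV infection on behaviors and other variables.

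Aim 1 Study Sample sets the exclusions: "Participants who have been tested for HIV within the last 6 months or who are known to be living with HIV infection are excluded" from Aim 1. Diagnosed people go elsewhere: "individuals who disclose a positive HIV status when Aim 1 eligibility is determined are considered for enrollment in Aims 2 and 3".

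Two further passages bear on the weights. Aim 1 Data Collection says the network-size items "assess the number of MSM and TW in the Yangon area the participant knows and has seen or spoken to in the last 6 months". Aim 1 Recruitment lets only some of those contacts extend a chain: "If eligible and after completing baseline study activities, the recruited participant may, in turn, become a recruiter".

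**The concern.** Network-size weighting corrects for unequal chances of being recruited. It does nothing for people whose chance of inclusion is zero. Here one excluded group, the known positives, is defined by the outcome being estimated, and the other, the recently tested, is likely to be related to it.

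The article gives a published Yangon prevalence in its Introduction. A weighted Aim 1 figure labeled as unbiased burden invites comparison with it, and a lower value could be read as a lower epidemic when it partly reflects who was screened out. The planned regressions raise the same issue: with known positives removed, their outcome is undiagnosed infection, whose correlates need not be those of all infection.

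The weights raise a second, conditional question. They are built from contacts in the whole MSM and TW network, while chains run only through eligible people.

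**Working it through.** **1. The plan's own figures.** The article derives no prevalence estimate. The nearest figure is the planning yield in Aim 1 Study Sample: 0.15 × 366 = 54.9, against 54 stated. That 15% is assumed for the sample and called conservative, so it is not an error, and nothing below depends on it being right.

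**2. Removing known positives.** Let P be prevalence among all MSM and TW, and k the share of people with HIV who are already diagnosed and so screened out. Those left comprise P(1−k) positives and 1−P negatives:

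prevalence among those left = P(1−k) / (1−Pk)

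The article gives no k, so I assume 20% to 50%. Example: 0.266 × 0.8 / (1 − 0.266 × 0.2) = 0.2128 / 0.9468 = 0.225.

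| P, and where it stands | k = 20% | k = 30% | k = 50% |
|---|---|---|---|
| 26.6% (Introduction, the upper figure for Yangon) | 22.5% | 20.2% | 15.3% |
| 15% (Aim 1 Study Sample, used here as if a population value) | 12.4% | 11.0% | 8.1% |
| 11.6% (Introduction, national) | 9.5% | 8.4% | 6.2% |

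Taken alone, this exclusion always lowers the figure: by 4.1 to 11.3 points in the first row, 2.6 to 6.9 in the second and 2.1 to 5.4 in the third.

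**3. Removing the recently tested.** Let t1 and t0 be the shares tested in the past 6 months among undiagnosed positives and among negatives (not given; assumed):

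P(1−k)(1−t1) / [P(1−k)(1−t1) + (1−P)(1−t0)]

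With P = 26.6%:

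| | t1 = t0 | t1 = 10%, t0 = 30% | t1 = 30%, t0 = 10% |
|---|---|---|---|
| k = 0 | 26.6% | 31.8% | 22.0% |
| k = 20% | 22.5% | 27.2% | 18.4% |
| k = 50% | 15.3% | 18.9% | 12.4% |

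The sign is not fixed. At k = 20%, one pattern more than cancels the loss of known positives and the other deepens it.

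**4. The network-size question.** Suppose the chance of inclusion is proportional to network size times the share e of contacts who are eligible, while the weight uses network size alone. With prevalence q among the eligible, and e1 and e0 the shares for positives and negatives, the weighted estimate tends to

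q·e1 / [q·e1 + (1−q)·e0]

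For q = 15%: equal shares give 15.0%, no bias; e1/e0 = 0.6/0.7 gives 13.1%; 0.7/0.6 gives 17.1%. The article gives no eligible shares, so these are illustrations.

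**5. Safeguards in the text.** Aim 1 Analytical Approach plans an exploratory look at how deep recruitment ran and whether recruitment introduced bias. That does not reach eligibility exclusions or the definition of network size. Nowhere does the article restate the prevalence target as undiagnosed infection or bring screened-out positives back into the estimate.

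**The case against.** The strongest reply is that the target is being imputed. The article's objectives concern testing uptake, staging and navigation, and none is total HIV prevalence. The sentence at issue concerns baseline characteristics, and *unbiased asymptotic* may only repeat a textbook property of the estimator. The Abstract describes those recruited as HIV uninfected, and the exclusions are openly stated. If the target is the eligible population, the exclusions define it and do not bias it.

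Much of that stands. With the target so defined, only the network-size question remains. But the article does not define it so: it attaches the property to disease burden and describes its results as those of MSM and TW populations. That is a statement to correct, not a detail left to a fuller document.

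A reader might also infer more than the article supports:

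- **That the estimate must understate burden by 4 to 11 points.** That range uses only the highest published figure and an assumed diagnosed share, and it leaves out the recent-test exclusion, which can offset it.
- **That the network-size mismatch is itself a bias.** It is one only if the eligible share of contacts differs by HIV status, which the article neither measures nor assumes away.
- **That stigma, access or testing history are distorted in a known direction.** Nothing in the article fixes one.
- **That the trial result is compromised.** The randomized comparison uses Fisher's exact test and does not rest on the weights.

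**Conclusion.** The claim of unbiasedness does not hold for HIV burden among MSM and TW. At best, Aim 1 estimates undiagnosed HIV among those not tested in the past 6 months. It depends on disclosure, since diagnosed people who do not disclose could still enter.

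As a measure of total burden, the loss of known positives alone turns 26.6% into 22.5% to 15.3%, or 15% into 12.4% to 8.1%, for an assumed diagnosed share of 20% to 50%. The net bias has no certain sign, because the recent-test exclusion and, conditionally, the network-size question can push either way. An accidental offset would not make the estimator unbiased.

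The consequence is confined to the descriptive estimates and the regressions on HIV infection. Sample size and the self-testing versus clinic-testing comparison are untouched.

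**What to change.** **Wording, at no cost and possible at any stage.**

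- State the target as undiagnosed HIV, and characteristics, among MSM and TW not known to be positive and not tested in the past 6 months.
- Remove the word unbiased.
- Interpret regressions on HIV infection as correlates of undiagnosed infection.
- Do not compare the figure with published total prevalence.

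**Optional, for remaining recruitment.** Record self-reported HIV status and network size for coupon holders who are screened out, and report an estimate over everyone screened. This is feasible: "Coupons are collected from recruited candidate participants at the study site at the time of eligibility screening", and Aims 2 and 3 Data Collection says the electronic system covers screening. The cost is a short addition to the screening form.

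Report it only as an approximate sensitivity analysis, because it does not give a valid population prevalence:

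- status is self-reported;
- screened-out people cannot recruit onward, so the weights are not justified for them;
- recruiters are paid only for eligible recruits who take part (Human Subjects Considerations), which favors passing coupons to eligible peers;
- recruitment began in November 2015 (Results), and the article describes no network-size data for those already screened out.

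### The unadjusted Fisher exact test for Aim 1 efficacy is valid and meets its planned 80% power, but it leaves precision unused that the same data could give

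*Protocol article*

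**What the plan says.** The primary hypothesis (protocol article, Aim 1 Analytical Approach) is that "a higher proportion of persons who are randomized to HIVST will complete HIV testing than those randomized to standard clinic-based testing". The efficacy analysis is named in the same section: "Standard contingency tables with Fisher exact test for significance is used to evaluate the efficacy of the intervention". The only stated role of baseline variables in the arm comparison is that "balance in potential measured confounders is assessed". The regression models in that section concern associations with HIV infection, not the effect of assignment.

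Aim 1 Data Collection describes a baseline questionnaire that includes "previous testing history and experiences, sexual and substance use risk profiles", together with demographics, stigma, cost and distance. Randomization follows the questionnaire and pretest counseling.

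Aim 1 Study Sample sets the size: "Assuming an error of .05 and 80% power to detect a 15% difference in acceptability between the 2 testing methods". The planning rates behind that difference are given there as "60% acceptability of clinic-based testing and 75% acceptability of self-testing", from which the authors conclude that "a sample of 330 (or 165 per group) is needed". The allowance for nonresponse comes next: "Upon factoring a 10% nonresponse in both testing methods, an effective sample size of 366 MSM and TW participants is calculated".

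**The concern.** Fisher's exact test conditions on both margins of the table. With binary data its attainable significance levels are discrete, so the true type I error lies below the nominal 5%, and some power is lost with it.

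A second and independent matter is that a comparison using assignment alone ignores baseline variables that may predict who completes testing. Adjusting for such variables narrows the interval around the treatment effect without adding participants.

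What is at stake is a few points of power and a tighter estimate. The validity of the comparison is not in question. The spare power would have some value because the planning rates describe acceptability, whereas the primary hypothesis concerns completion, for which no rates are stated.

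**Working it through.** **Inputs from the protocol article.** Rates 0.60 and 0.75, error 0.05, power 80%, 165 per group, 10% nonresponse, total 366. Sidedness is not stated; two-sided is inferred below.

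**Step 1: reproduce the sample size.** With mean rate 0.675 and difference 0.15:

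- Uncorrected: n = [1.96·√(2·0.675·0.325) + 0.842·√(0.60·0.40 + 0.75·0.25)]² / 0.15² = (1.298 + 0.550)² / 0.0225 ≈ 151.9, so 152 per arm.
- Continuity-corrected: n = (151.9/4)·[1 + √(1 + 4/(151.9·0.15))]² ≈ 164.9, so **165 per arm**, 330 in total. This matches the protocol.
- One-sided calculations give 120 (133 with the correction) and do not match.
- 330/0.90 = 366.7, against the stated 366, which is a rounding difference.

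The continuity-corrected formula approximates Fisher's test, so the stated size already allows for its conservatism.

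**Step 2: true size and power of the unadjusted tests.** All 2×2 tables at 165 per arm were enumerated exactly, two-sided at nominal 0.05.

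| Test | Size at common rate 60% | 67.5% | 75% | 90% | Power, 60% vs 75% |
|---|---|---|---|---|---|
| Fisher exact | 0.038 | 0.039 | 0.038 | 0.031 | 80.5% |
| Mid-P | 0.049 | 0.050 | 0.049 | 0.046 | 83.3% |
| Uncorrected chi-square | 0.050 | 0.051 | 0.050 | 0.051 | 83.5% |

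Over common rates from 50% to 98%, Fisher's size never exceeds 0.042. The choice of test alone costs 83.5 − 80.5 = 3 points, or 165 − 152 = 13 per arm in sample-size terms. If all 183 per arm (366/2) are analyzed, the powers are 84.5% (Fisher) and 87.0% (chi-square). At assumed completion rates of 80% versus 90% with 165 per arm, they are 68.0% and 72.9%.

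**Step 3: covariate adjustment.** Let R² be the share of outcome variance explained by the covariates. Adjustment acts roughly like a sample of n/(1 − R²) per arm:

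Power = Φ{[0.15·√(n/(1 − R²)) − 1.96·√(2·0.675·0.325)] / √(0.60·0.40 + 0.75·0.25)}

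Example at R² = 0.05: 165/0.95 = 173.7, so (0.15·13.18 − 1.298)/0.654 ≈ 1.038 and Φ = 85.0%.

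| Assumed R² | Power by formula | Simulated power, standardized risk difference |
|---|---|---|
| 0.02 | 83.9% | not run |
| 0.05 | 85.0% | 85.1% |
| 0.10 (simulated at 0.11) | 86.9% | 87.0% |
| 0.20 (simulated at 0.19) | 90.5% | 89.3% |

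The simulations used 4,000 trials per setting. The type I error of the adjusted analysis was 0.046 to 0.053, against 0.037 to 0.042 for Fisher in the same runs, so an inflated error rate does not explain the gain.

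**The case against.** The strongest reply is that nothing is broken. The sample size and the test agree: 165 per group is the number a Fisher-type calculation gives, and Fisher then yields 80.5% against a target of 80%. Fisher also holds type I error at or below 5%, which a model-based analysis does only approximately. All of this stands.

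The adjustment gain is also uncertain. No section calls any baseline item prognostic for completing a test. People tested in the previous 6 months or known to be HIV positive are excluded, which narrows variation in testing history. The article itself describes the local identity categories as overlapping, so MSM/TW identity may be a weak covariate. At R² = 0.02 the adjusted power of 83.9% is practically that of a plain chi-square test. This limits the promised gain but does not put adjustment below Fisher.

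Recruitment was under way when the article was written, so a change of primary analysis needs a record that it was made without sight of results by arm. This also stands.

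Some stronger readings are tempting and not supported:

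- A reader might infer that the low error rate results from the missing adjustment. It comes from Fisher's discreteness; the unadjusted chi-square and mid-P tests are already close to 5%.
- A reader might infer that chance imbalance would bias the result. In a randomized comparison it is covered by the test's error rate; adjustment buys precision.
- A reader might fault the absent confidence interval or the unstated use of the balance check. An article may leave both to an analysis plan that is not shown, and the arm proportions in the contingency tables already imply a risk difference.

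**Conclusion.** The point holds as an inexpensive improvement in efficiency. The named test gives up about 3 points of power through its conservatism (80.5% versus 83.5%). Adjustment would bring power to about 84% to 89%, a total gain of roughly 3 to 9 points over Fisher, if the covariates explain about 2% to 20% of outcome variance.

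Confidence is high for the Fisher and chi-square figures, which are exact at the stated rates, and moderate for the adjustment gain, which rests on an assumed R². All powers at 60% versus 75% borrow acceptability rates for a completion endpoint.

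The documents do not support calling the trial underpowered or the test invalid. Nor should fewer participants be promised: Aims 2 and 3 Study Sample also ties the overall size to the numbers needed for those aims.

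**What to change.** Before outcomes by arm are examined, define the primary Aim 1 analysis as the intention-to-treat risk difference in test completion, HIVST minus clinic-based testing, with a 95% confidence interval. Obtain it by standardization from a logistic model with assignment and a short fixed list of covariates recorded before randomization, and use a robust standard error. Candidates already collected are previous HIV testing, MSM/TW identity and distance; the list should be settled on expected prognostic value and not on observed imbalance. Keep Fisher's exact test as a supporting analysis.

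If the team prefers no covariates, an uncorrected chi-square or mid-P test would still recover about 3 points.

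No new data or participants are needed. The costs are a dated, documented change to the analysis during ongoing recruitment, and a type I error that is approximately 5% rather than guaranteed at or below 5%.
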